### 3.7 Sample size and power

Of the primary outcome measures the decrease in diarrhoea is the most difficult to catch. We have based our sample size calculation on the expected reduction in cases of diarrhoea (at the age of 3 months) over the last two weeks of one third from 12% to 8%. With a 95% confidence (alpha error 0.05) and power of 80%, and an average number of infants of 35 per randomised community, and a coefficient of variation between the communities of 0.3, we will need to randomise 48 communities in each arm – a total of 96 communities, see table below.

|                                                                         |    | Increase in EBF from
20 to 40% | Decrease in
diarrhoea |
|-------------------------------------------------------------------------|----|-----------------------------------|--------------------------|
| Proportion in the intervention group                                    | P1 | 0.4                               | 0.08                     |
| Proportion in the control group                                         | P2 | 0.2                               | 0.12                     |
| Percentage point for alfa error = 0.05                                  | z1 | 1.96                              | 1.96                     |
| Percentage point for beta error = 0.20                                  | z2 | 1.28                              | 1.28                     |
| Number of individuals in each community                                 | n  | 35                                | 35                       |
| coefficient of variation of proportions among communities in each group | k  | 0.4                               | 0.3                      |
| Average of P1 and P2                                                    | P  | 0.3                               | 0.1                      |
| Number of communities needed per arm                                    | C  | 12                                | 48                       |

This will include 420 infants in each arm in each country, a total of 840 children per country and all in all 3360 children studied across the four sites. This sample size will very accurately give us the increase in EBF and be able to document the above decrease in diarrhoea morbidity.

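### The sample-size table labels z2 = 1.28 as the point for 80% power, but it is the point for 90%; the printed 48 and 12 communities per arm follow from 1.28, so the stated power is too low

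*Protocol*

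**What the plan says.** All the planning figures stand in protocol section 3.7.

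- **Error rates in the text:** "With a 95% confidence (alpha error 0.05) and power of 80" per cent.
- **Diarrhoea effect:** a reduction "over the last two weeks of one third from 12% to 8" per cent.
- **Cluster size and variation:** "an average number of infants of 35 per randomised community" and "a coefficient of variation between the communities of 0.3". The EBF column of the table uses 0.4 for the latter.
- **Result for diarrhoea:** "we will need to randomise 48 communities in each arm – a total of 96 communities". The EBF column gives 12 per arm for a rise from 20% to 40%.
- **Total:** "all in all 3360 children studied across the four sites".

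The table row "Percentage point for beta error = 0.20" carries z2 = 1.28 in both columns. No other section states a power or explains z2. Section 3.6 randomises 24 clusters per site. Section 3.11 makes the EBF comparison specific to each site and the diarrhoea comparison a whole-study one.

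**The concern.** A row label and its value disagree. The normal point that leaves 0.20 in the tail is 0.842. The value 1.28 leaves 0.10 (its cumulative probability is 0.8997). Sidedness does not explain this: z1 = 1.96 is right for a two-sided 0.05, and the beta point does not depend on the number of sides.

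If the slip were confined to the label, it would be cosmetic. If it went into the arithmetic, the stated power and the stated number of communities do not belong together, and these are the main planning figures for funders, ethics committees and readers.

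There is a practical side as well. The calculation has no allowance for loss: the total counts 35 infants in every community. The gap between 80% and the power actually delivered is then the only reserve, and the text does not show it. Someone who corrected z2 alone and recomputed could remove that reserve without noticing.

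**Working it through.** **Inputs (all from the section 3.7 table).** z1 = 1.96; n = 35. Diarrhoea: P1 = 0.08, P2 = 0.12, k = 0.3. EBF: P1 = 0.4, P2 = 0.2, k = 0.4. The protocol does not print its formula. I use the standard one that takes exactly these inputs (Hayes–Bennett):

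C = 1 + (z1 + z2)² × [P1(1−P1)/n + P2(1−P2)/n + k²(P1² + P2²)] / (P1 − P2)²

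**Variance terms (the square bracket).**

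- Diarrhoea: (0.0736 + 0.1056)/35 + 0.09 × (0.0064 + 0.0144) = 0.005120 + 0.001872 = 0.006992. Divided by 0.04² = 0.0016, this is 4.370.
- EBF: (0.24 + 0.16)/35 + 0.16 × (0.16 + 0.04) = 0.011429 + 0.032000 = 0.043429. Divided by 0.2² = 0.04, this is 1.0857.

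**Reproducing the printed counts.** (1.96 + 1.28)² = 10.498 and (1.96 + 0.84)² = 7.840.

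| z2 | Diarrhoea, C per arm | EBF, C per arm |
|---|---|---|
| 1.28 | 1 + 10.498 × 4.370 = 46.9 | 1 + 10.498 × 1.0857 = 12.4 |
| 0.84 | 1 + 7.840 × 4.370 = 35.3 | 1 + 7.840 × 1.0857 = 9.5 |
| Printed | 48 | 12 |

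Using the table's average P in the binomial term moves the diarrhoea figures only to 47.0 and 35.4. Over the variants tried (average P, and an added constant of 0, 1 or 2), the largest diarrhoea count at 80% power is 36.4. Both printed counts fit 1.28 to within about one cluster; neither fits 0.84.

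**Power actually delivered.** Inverting the formula, power = Φ(√[(C − 1)/R] − 1.96), where R is the ratio above.

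- Diarrhoea, C = 48: √(47/4.370) − 1.96 = 1.320, so power is 90.6%.
- EBF in one country, C = 12: √(11/1.0857) − 1.96 = 1.223, so power is 88.9%.

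**How far the reserve stretches for diarrhoea (48 per arm, k = 0.3).** The cluster sizes below 35 are my assumptions, chosen to show the range.

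| Infants analysed per community | Power |
|---|---|
| 35 | 90.6% |
| 30 | 87.2% |
| 25 | 82.2% |
| 24 | 81.0% |
| 23 | 79.7% |
| 20 | 75.0% |

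This depends on k. With 35 infants per community, an assumed k of 0.4 gives about 85% and 0.5 gives about 77%.

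**What a true 80% on both outcomes would need.** EBF is judged in each country, so it needs 9.5, rounded up to 10 per arm per country: 40 per arm over four countries, 80 communities, 80 × 35 = 2800 infants. At C = 10, EBF power is 82.1%; at C = 40, diarrhoea power is 84.8%. Taking the diarrhoea count alone (36 per arm) leaves 9 per arm per country, and EBF power is then 77.5%.

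**The case against.** The best defence is that the slip is harmless. It runs in the safe direction: on the protocol's inputs both primary outcomes exceed the stated 80%, and the remedy changes no number randomised, no outcome and no analysis. That stands, and it sets the weight of the point.

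A second objection is that the formula is inferred and the match is not exact. With 1.28 it gives 46.9 rather than 48, and the EBF figure of 12.4 would round up to 13 where the table prints 12. The total of 48 is also simply 12 per arm in four countries. This stands too, but it does not rescue the stated power: the residual is about one cluster, against a gap of 12 or more between 48 and anything obtained at 80%.

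Two stronger readings are tempting, and the documents support neither.

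- A reader might infer that 80% power needs only 36 communities per arm, so that 24 communities and 840 infants are surplus, and that the table could be restated with 10 and 36. That treats diarrhoea as the only constraint. Section 3.11 makes EBF a site-specific primary outcome, and 36 per arm falls short for it in each country. The difference from a design with 80% on both outcomes is 96 − 80 = 16 communities and 3360 − 2800 = 560 infants.
- A reader might also infer that a faulty power calculation means a faulty design. On the stated inputs it does not.

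**Conclusion.** The point holds as a wrong stated figure, not as a design failure. Section 3.7 claims 80% power and beta = 0.20 but computes with the beta = 0.10 point. With the printed numbers of communities, power is about 90.6% for diarrhoea across the study and about 89% for EBF in each country.

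This rests on the protocol's own proportions, on 35 infants analysed in every community, on k = 0.3 and 0.4, and on the standard formula being close to the one used, which the match to within about one cluster supports. The margin above 80% is real only while those inputs hold. For diarrhoea it is used up when fewer than 24 infants per community are analysed at k = 0.3, or, with 35 infants, at a k somewhere between 0.4 and 0.5.

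**What to change.** Keep 96 communities. In section 3.7:

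1. Change the table row from beta = 0.20 to beta = 0.10, leaving z2 = 1.28.
2. Change the text from 80% to about 90% power, with 35 infants analysed per community.
3. Add one sentence: with 48 communities per arm and k = 0.3, power for the fall in diarrhoea from 12% to 8% stays at or above 80% provided at least 24 infants per community are analysed at 3 months.
4. Print the formula, so that the counts can be reproduced.

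Do not correct z2 to 0.84 and carry 36 per arm forward. If the sponsor did want to plan at 80% on both outcomes, the consistent figure is 10 per arm per country (40 per arm in total).

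The cost is protocol wording only; recruitment, randomisation and analysis are unchanged.

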### **3.8 Recruitment procedure**

The recruitment procedure will be adapted to the local circumstances. In the most common case, each cluster will have a recruiter ("pregnancy monitor") who will be a mature woman of good reputation living within the cluster. The pregnancy monitors will inform the research centre about pregnant women that may be eligible to participate in the study. A data collector / research assistant will be sent to visit the woman to ascertain eligibility, obtain consent to participate in the study and conduct the recruitment interview.

In South Africa, the recruitment of women will be done at the health facility in the antenatal clinic, where a data collector / research assistant will interview the woman to ascertain eligibility, obtain consent to participate in the study and conduct the recruitment interview.

All mothers in the selected and randomised clusters are a priori selected and randomised. In order to carry out an intention-to-treat analysis, it is important to minimise the loss of eligible mothers. For mothers declining to participate, minimal socio-demographic information should preferably be collected.

### **3.9 Participant flow**

Pregnant women will be identified by a recruiter ("pregnancy monitor")

The pregnancy monitors will inform the research centre about the pregnant woman

A data collector / research assistant will visit the woman to ascertain eligibility

Consent to participate in the study will be obtained

The recruitment interview will be conducted

The peer-counsellor is informed about the woman and visits her to make an appointment

The woman is visited by the peer-counsellor who provides the first counselling session

The woman gives birth

The woman is revisited by the peer-counsellor after birth who provides the 2nd counselling session

The woman is revisited by the peer-counsellor after birth who provides the 3rd counselling session

A data collector / research assistant will visit the woman for the week 3 interview

The woman is revisited by the peer-counsellor after birth who provides the 4th counselling session

A data collector / research assistant will visit the woman for the week 6 interview

The woman is revisited by the peer-counsellor after birth who provides the 5th counselling session

A data collector / research assistant will visit the woman for the week 12 interview

A data collector / research assistant will visit the woman for the week 24 interview

### **3.10 Intervention and standard care**

The study will have two arms: An intervention arm and a standard care arm.

#### **Intervention arm**

The infants in the intervention arm will be treated similarly to the infants in the standard care arm except for the peer-counselling on exclusive breastfeeding. After the informed consent, the mothers in the intervention arm will be visited by a peer-counsellor on 1 occasion before delivery, at 0.5-1, 2, 4, 8 (and 16 weeks) postnatally. The peer-counsellor will deliver messages on the advantages of EBF; provide support for EBF, provide simple technical information for overcoming constraints, provide referral of more complicated problems, and provide reminders and encouragement to remain/return to EBF.

### **3.11 Primary outcome**

The outcome measures in this study are:

- EBF prevalence at 3 months. In the intervention group receiving peer counselling, we expect an raise in the proportion of infants who are exclusively breast-fed from birth through 3 months by 20 percentage points from baseline of 20% (although we will recommend 6 months, we do not expect many to achieve this in any group). This measure will be site specific.
- The impact of increased EBF on infant morbidity, growth and micronutrient status requires a larger sample. We have decided to use active surveillance for infant morbidity and we use the following outcome measures, which will be calculated for the whole study:
- Decrease in diarrhoea. In the intervention group we expect a reduction of one third from an estimated baseline of 12 % diarrhoea incidence in the last 2 weeks (to 8% in the intervention group).

### **3.12 Secondary outcomes**

- Improved growth up to 6 months of age.
- Micronutrient status. We have decided to assess infants in three of the sites, Burkina Faso, Uganda and Zambia. If no major deviation is seen in such a sample, we conclude there are no pertinent micronutrient deviations.

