### **Safety**

Breastfeeding is safe and acceptable all over the world. The risk of HIV infection will be dealt with in the usual way as a part of voluntary counselling and testing for HIV. That is, the women will be offered HIV testing and if found HIV-positive they will make an informed choice after being provided with information on the advantages and disadvantages of each type of feeding. In

addition, we will be training and hiring lactation management consultants and linking them to the local health centres. They (and to a lesser extent the peer counsellors) will assist mothers to use the correct latching on, positioning and other factors to reduce the risk of breast damage with consequent increase in the risk of HIV transmission. Finally, the usual prophylaxis with nevirapine to the mother at the time of delivery and to the infant within two days after delivery will be offered. There is accordingly no risk of any serious adverse effects from participation in the PROMISE study.

We suggest to draw 5 ml of blood from a number of infants on two occasions during the first year of life. This is to clarify if exclusive breastfeeding up to 6 months of age may have a negative impact on the micronutrient status of the infant. In some instances the blood sample will be beneficial for the infant itself. For instance, if the mother is HIV-positive and the family consents, these samples will be analysed for HIV and if the child has become HIV-positive, adequate care will be provided for the child. The blood will also be analysed for micronutrients and if a deficit is found, adequate supplementation will be given. In such instances, the ethical problem is small. But for many children, this blood sample will not benefit their own health directly and therefore it may be questioned whether it is justifiable to perform these blood samplings on infants. The problem is that the research question cannot be answered by studying adults. The alternative in this particular case is in fact not to attempt to answer the question.

WHO has called for an answer to this particular question, and we therefore consider the ethical dilemma as solvable. But of course this question will be scrutinised in all the medical ethics committees related to the involved institutions and we will of course follow their advice.

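### The micronutrient rule takes not seeing a major deviation as showing that no pertinent one exists, with no margin or confidence limit

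*Protocol*

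**What the plan says.** Section 3.12 of the protocol lists micronutrient status as a secondary outcome. It limits the assessment to three of the four countries ("We have decided to assess infants in three of the sites, Burkina Faso, Uganda and Zambia") and then states the conclusion rule: "If no major deviation is seen in such a sample, we conclude there are no pertinent micronutrient deviations". It defines neither *major* nor *pertinent*, and names no comparator, margin or interval.

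Other sections bear on the rule:

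- **Objectives (2.2).** Micronutrients appear three times: as an effect of the trial (objective 1), in relation to actual feeding pattern (objective 2), and as a description of EBF infants up to six months (objective 3).
- **Primary outcome (3.11).** The expected rise is in infants "exclusively breast-fed from birth through 3 months by 20 percentage points from baseline of 20" per cent, that is, 40% against 20%. On EBF for 6 months the protocol says "we do not expect many to achieve this in any group". The same section remarks: "The impact of increased EBF on infant morbidity, growth and micronutrient status requires a larger sample".
- **Safety (under 5.0).** The plan is to "draw 5 ml of blood from a number of infants on two occasions during the first year of life", in order to clarify whether EBF up to 6 months harms micronutrient status. It adds that "if a deficit is found, adequate supplementation will be given".
- **Sample size (3.7).** The calculation covers EBF and diarrhoea only.

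**The concern.** The rule moves from a large deviation not being seen to no deviation that matters being present. The two adjectives set different thresholds, and the step between them is an inference that an imprecise sample cannot support. A wide interval around a small estimate and a narrow interval around zero would give the same conclusion, although only the second is evidence of safety.

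This matters for a secondary outcome because section 1.1 gives uncertainty about micronutrient status as one of two major reasons why EBF is not already promoted on a large scale. The Safety text also justifies taking blood from infants, many without direct benefit, by the need to answer this question. A statement of no pertinent deviation would be read as reassurance whether or not the data could have shown harm.

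Supplementation adds a lesser problem. Infants found deficient are treated, so a later sample from them can understate the deficit.

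**Working it through.** The protocol gives no sample size, margin or power for micronutrients, so there is no figure of its own to reproduce. The check asks what the rule could show under each reading.

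**Inputs from the protocol.** EBF at 3 months is 40% in the intervention arm and 20% in the control arm (3.7, 3.11). With 840 children per country (3.7), three countries give at most 3 × 840 = 2,520 infants, or 1,260 per arm.

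**Assumed inputs, not in the protocol.** Deficiency is 30% without EBF and 45% with EBF. The sample is 150 or 400 infants per arm. Clustering is ignored, which flatters precision. Power is for a two-sided test at 5%.

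**Reading A: between arms (objective 1)**

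1. Control arm: 0.20 × 45 + 0.80 × 30 = 33%.
2. Intervention arm: 0.40 × 45 + 0.60 × 30 = 36%.
3. Difference: 0.20 × 15 = 3 points, a five-fold dilution (1/0.20).
4. SE = √[(0.33 × 0.67 + 0.36 × 0.64)/m] = √(0.4515/m).

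| Infants per arm (m) | SE (points) | 95% CI half-width, 1.96 × SE (points) | Power for 3 points |
|---|---|---|---|
| 150 | 5.49 | 10.8 | 8.5% |
| 400 | 3.36 | 6.6 | 14.5% |
| 1,260 (every infant in three countries) | 1.89 | 3.7 | about 35% |

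5. For 80% power at 3 points: (1.96 + 0.84)² × 0.4515/0.03² ≈ 3,900 per arm, above the ceiling of 1,260.

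The 20-point gap applies at 3 months. If few infants in any group reach 6 months, the gap there is probably smaller and the dilution greater.

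**Reading B: by actual feeding pattern (objective 2)**

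There is no dilution here. The same 30% and 45% are used, with SE = √(0.45 × 0.55/n₁ + 0.30 × 0.70/n₀), where n₁ infants are EBF and n₀ are not.

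| Total infants | Share EBF at sampling | n₁ / n₀ | SE (points) | Power for 15 points |
|---|---|---|---|---|
| 300 | 30% (mean of 40% and 20%) | 90 / 210 | 6.1 | 69% |
| 800 | 30% | 240 / 560 | 3.75 | 98% |
| 300 | 10% (assumed, nearer 6 months) | 30 / 270 | 9.5 | 35% |
| 800 | 10% | 80 / 720 | 5.8 | 73% |

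**Reading C: within EBF infants (objective 3)**

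The number still EBF at 6 months is expected to be small. If 10 such infants were sampled (assumed) and none was deficient, the exact upper 95% limit for the true prevalence would be 1 − 0.025^(1/10) = 0.31. The rule would report no pertinent deviation while a prevalence of up to 31% remained compatible with the data.

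**Supplementation.** The Safety text allows two draws in the first year without fixing their timing. The first draw cannot be affected. Only measurements made after a deficit was found and treated can be, and the size of the effect cannot be derived from the protocol.

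**The case against.** The strongest reply is that section 3.12 specifies neither a between-arm comparison nor a significance test. A major deviation could equally mean departure from normal status, and section 1.3 frames the gap in knowledge partly in those terms. Dilution then affects only objective 1, and Reading B shows that with many EBF infants a 15-point difference would usually be detected. This stands, and it limits the size of the claim.

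A reader might infer from Reading A that the rule would miss a real effect about nine times in ten, or would give a false all-clear whatever the truth. The protocol does not support either inference. The figures rest on assumed rates and sample sizes, and they equate not seeing a deviation with p > 0.05, which the protocol never says. If there is no deviation the conclusion is correct, and a very large one could still be seen.

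A reader might also count the missing subsample size as an error in itself. Sections 3.13 and 3.15 leave analysis detail to standard operating procedures, and a statistical analysis plan may set the size and cut-offs. That omission is not the finding. Nor is it established that supplementation distorts the 6-month result, since the timing of the draws is not stated.

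None of this repairs the sentence. A later document could add a sample size or a threshold, but the protocol would still commit the trial to concluding absence from not seeing.

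**Conclusion.** The point holds as an error in a stated conclusion rule. Section 3.12 infers no pertinent deviation from no major deviation seen, without a margin or confidence limit, and this inference is invalid whichever comparison is meant.

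The size depends on the reading. Between arms, the five-fold dilution follows from the protocol's own 20-point gap. The half-widths of 10.8 and 6.6 points and the power of 8.5% and 14.5% rest on the assumed 30% and 45%, the assumed 150 and 400 per arm, and no clustering. By feeding pattern, power in the illustration runs from 35% to 98%, according to how many infants are EBF at sampling. Within EBF infants, precision is limited by the few expected to reach 6 months.

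Severity is should-fix: the outcome is secondary, and the primary outcomes, randomisation and trial size are not affected.

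**What to change.** Replace the sentence in section 3.12 with wording to this effect: *For each marker, report the cluster-adjusted difference between arms with its 95% CI and, as a secondary comparison labelled non-randomised, the difference by actual feeding pattern. Conclude no pertinent deviation only if the CI excludes a margin fixed beforehand; otherwise report the result as inconclusive.*

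The label is needed because infants who are and are not EBF may differ for other reasons, so that comparison is open to confounding and reverse causation.

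For supplementation, base the conclusion on measurements taken before any study-triggered supplementation, or add a sensitivity analysis for infants supplemented after the first draw. Counting all of them as deficient at the second draw is one possible analysis but a contestable one, so it should not be the only one. The commitment to treat deficits is not in question.

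The cost is a change of wording and one margin per marker, set before the data are seen. No extra blood or infants are needed to report the result this way. The downside is that the between-arm result may well be inconclusive: in the illustration, even all 1,260 infants per arm give a half-width of 3.7 points against a 3-point difference.
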